
## Sleep studies

Nocturnal polysomnography will be performed according to standard techniques as described previously. In addition to central EEG derivations, EOG and submental EMG, measurements include calibrated respiratory inductive plethysmography (RespiratracePT, Nims, Miami Beach, USA), pulse oximetry, end-tidal (CapnoCheck Plus, ResMed, Basel Switzerland) and transcutaneous PCO2 (Tosca, Radiometer, Basel, Switzerland), pulse transit time, nasal pressure swings, oral thermistor, NIRS of cerebral tissue oxygenation from 2 miniaturized frontal sensors, bilateral sub costal surface EMG of the diaphragm to assist in differentiation of obstructive from central apnea/hypopnea. Sleep and arousals will be scored according to standard criteria as described by Rechtschaffen und Kales and by the American Academy of Sleep Medicine guidelines. An apnea or hypopnea will be scored if the amplitude of the nasal pressure swings or the sum signal of the respiratory inductive plethysmography falls below 50% of baseline during the previous 2 minutes for >10 seconds. Obstructive will be differentiated from central events based on rib cage-abdominal asynchronous and paradoxical motion, deformations of the nasal pressure curve suggesting inspiratory flow limitation, and diaphragmatic surface EMG. The apnea/hypopnea and oxygen desaturation index (SpO2 dips >3%) will be computed as mean number of events/h.

## 7 ASSESSMENT OF SAFETY

### 7.1 SAFETY VARIABLES

Adverse events or reactions will be evaluated by daily physical examinations, evaluation of questionnaires, through the acquisition of the variables described above at the time points listed in table 3 and through voluntary report at any time during the study.

### 7.2 FOLLOW-UP OF PATIENTS AFTER ADVERSE EVENTS

Patients will be followed until the event resolves or until 12 weeks after the event is reported.

### 7.3 ADVERSE EVENTS

#### Adverse Event (AE)

Per the International Conference of Harmonisation (ICH), an AE is any untoward medical occurrence in a patient or clinical investigation subject underwent an interventional procedure, which does not necessarily have a causal relationship with the treatment. An AE can therefore be any unfavourable and unintended sign (including an abnormal laboratory finding), symptom, or disease temporally associated with the use of a medicinal product, whether or not considered related to the study-intervention. Pre-existing conditions which worsen during a study are to be reported as AEs. Each participant will be examined according to checklists and with questionnaires during the study. Adverse events will be recorded in prepared forms and checklists (see CRF). Adverse events that occur intermittently should be recorded as one AE. Adverse events should be collected and reported for up to 14 days after the study intervention.

Intensity: All clinical AEs encountered during the clinical study will be reported on the AE page of the CRF. Intensity of AEs will be graded on a four-points scale (mild, moderate, severe, life-threatening) and reported in detail in the CRF.

**Mild** – Discomfort noticed but no disruption of normal daily activity.

**Moderate** – Discomfort sufficient to reduce or affect daily activity.

**Severe** – Inability to work or perform normal daily activity.

**Life threatening** – Represents an immediate threat to life.

Study intervention – Adverse Event Relationship: Relationship of the AE on the treatment should always be assessed by the investigator. AE categories for determining relationship to altitude:

**PROBABLE** (must have first three)

This category applies to those AEs which are considered, with a high degree of certainty, to be related to the altitude. An AE may be considered probable, if:

1. It follows a reasonable temporal sequence from altitude.
2. It cannot be reasonably explained by the known characteristics of the subject's clinical state or environmental administered to the subject.
3. It follows a known pattern of response to the suspected intervention.

**POSSIBLE** (must have first two)

This category applies to those AEs in which the connection with the altitude appears unlikely but cannot be ruled out with certainty. An AE may be considered possible if, or when:

1. It follows a reasonable temporal sequence from altitude.
2. It may have been produced by the subject's clinical state or environmental factors administered to the subject.

3. It follows a known pattern of response to the suspected intervention

REMOTE (must have first two)

In general, this category is applicable to an AE which meets the following criteria:

1. It does not follow a reasonable temporal sequence from altitude.
2. It may readily have been produced by the subject's clinical state or environmental factors administered to the subject.
3. It does not follow a known pattern of response to the suspected intervention.

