### **10.2 REPORTING PROCEDURES**

All adverse events will be reported. Depending on the nature of the event the reporting procedures below should be followed. Any questions concerning adverse event reporting will be directed to the Principal Investigator in the first instance. Non SAEs, whether expected or not, will be recorded. SAE's form will be completed and forwarded to the Principal Investigator within 24 hours. The Principal Investigator will assess whether the event is 'related', i.e. resulted from the administration of any of the research procedures; and 'unexpected', i.e. an event that is not listed in the protocol as an expected occurrence.

Reports of suspected related and unexpected SAEs (SUSARs) will be submitted within 15 days and within 7 days for fatal or life-threatening SUSARs, respectively, of the investigator becoming aware of the event, to the Ethics Committee using the CIOMS format.

The Ethics committee will be informed about changes in the protocol, interim and final reports will be delivered.

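### The adverse-event causality scale in section 7.3 is tied to altitude although relationship to treatment must be assessed, and read strictly it leaves some events without a category

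*Protocol*

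**What the plan says.** Protocol section 7.3, under Adverse Event (AE), states: "Relationship of the AE on the treatment should always be assessed by the investigator". The scale that follows at once is headed "AE categories for determining relationship to altitude" and has three categories.

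- PROBABLE carries the rule "must have first three". Its criteria are "It follows a reasonable temporal sequence from altitude", "It cannot be reasonably explained by the known characteristics of the subject's clinical state or environmental administered to the subject" and "It follows a known pattern of response to the suspected intervention".
- POSSIBLE requires its first two criteria: reasonable timing from altitude, and that the clinical state or environmental factors may have produced the event. A known pattern is listed third and is not required. The category is described as covering links that look unlikely but cannot be excluded.
- REMOTE requires its first two criteria: "It does not follow a reasonable temporal sequence from altitude", and that the clinical state or environment may readily have produced the event. Absence of a known pattern is listed third and is not required.

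There is no category for unrelated or unclassifiable events.

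The Serious Adverse Event (SAE) part of section 7.3 foresees skin irritation from sensors, and pain and haematoma from arterial puncture. It also has SAEs reported immediately to the ethics committee.

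Section 10.2 uses a different test. For an SAE, the Principal Investigator decides whether it is related, meaning that it "resulted from the administration of any of the research procedures", and whether it is unexpected, meaning not listed in the Protocol. Suspected related and unexpected SAEs go to the ethics committee within 15 days, or within 7 days if fatal or life-threatening. Non-serious events need only be recorded.

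**The concern.** The instruction and the scale name different exposures. The instruction asks about the treatment; the scale asks about altitude. In phase 1 altitude is the exposure under study, so the two roughly coincide. In phase 2 the randomised contrast is nocturnal oxygen against sham, and patients are at altitude in both periods. Grading an event against altitude then says nothing about the concentrator, the cannula or the oxygen. The same holds for study procedures, some of which take place before any altitude exposure.

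The categories also appear to leave holes. An event with plausible timing, no competing explanation and an unfamiliar presentation is one that an investigator would want to flag. The scale as worded does not clearly accept it.

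At stake is the meaning of the recorded causality grade. For non-serious events it is the only causality judgement that the Protocol specifies. For serious events a second judgement exists under section 10.2, but the two rest on different exposures and nothing links them.

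**Working it through.** The Protocol gives no figure on this point, so the check is one of logic.

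**Step 1: which exposure is graded.**

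| Source of harm | Where the Protocol places it | Timing criterion in 7.3 | Applicable scale in 7.3 |
|---|---|---|---|
| Altitude | Both phases | From altitude | Yes |
| Nocturnal oxygen or sham | Phase 2, both periods at altitude (section 4.2, Table 4) | From altitude, met in either period | None |
| Study procedures | All locations, including 490 m | From altitude | None |

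On the last row, every phase 2 patient is assessed at 490 m first (Table 4), as are phase 1 COPD sequences A and B (Table 2) and PH/ILD sequence A (Table 2a). Arterial blood gases are also taken at screening (section 5.1). A puncture haematoma arising there cannot follow altitude. It is either REMOTE, if the procedure is stretched into the environmental factors of criterion 2, or ungraded. Neither records that a study procedure caused it.

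**Step 2: whether the categories are exhaustive.** Let T = reasonable timing from altitude, E = another explanation exists, K = known pattern. The required criteria then read:

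- PROBABLE = T and not E and K
- POSSIBLE = T and E (K free)
- REMOTE = not T and E (K free)

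There are 2 × 2 × 2 = 8 combinations.

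| T | E | K | Category |
|---|---|---|---|
| yes | yes | yes | POSSIBLE |
| yes | yes | no | POSSIBLE |
| yes | no | yes | PROBABLE |
| yes | no | no | none |
| no | yes | yes | REMOTE |
| no | yes | no | REMOTE |
| no | no | yes | none |
| no | no | no | none |

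Placed: 1 + 2 + 2 = 5. Unplaced: 8 − 5 = 3. The fourth row is the unexplained, atypical event that follows altitude. It fails PROBABLE on criterion 3 and POSSIBLE on criterion 2, and it fails REMOTE on both required criteria.

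**Step 3: sensitivity to how criterion 2 is read.** The table treats E as a strict yes or no. The wording differs by category: PROBABLE speaks of what cannot reasonably explain the event, POSSIBLE of what may have produced it, REMOTE of what may readily have produced it. If POSSIBLE's criterion is taken as always met, the fourth row becomes POSSIBLE and 2 of 8 remain unplaced. If REMOTE's is also taken as always met, none remain. On either loose reading, the third row satisfies both PROBABLE and POSSIBLE, so a gap is exchanged for an overlap. The unplaced count therefore runs from 0 to 3, depending on a reading that the Protocol does not fix.

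**Step 4: whether section 10.2 depends on this scale.** It does not. Its test of relatedness needs neither timing from altitude nor a known pattern, and it does not cite the three categories.

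**The case against.** A reader might infer that harms of oxygen or of procedures, and the most unexpected reactions, cannot be classified as related and so escape expedited reporting. The documents do not support that. Section 10.2 has the Principal Investigator judge an SAE against any research procedure without using the 7.3 scale, and section 7.3 sends SAEs to the ethics committee without a condition of relatedness. Treating oxygen as one of the research procedures is an interpretation, but a natural one.

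A reader might also infer that phase 2 could not compare harms of oxygen and sham. That does not follow either. Phase 2 is randomised, double-blind and cross-over, so events can be compared by randomised period after unblinding, with no individual causality grade. A blinded investigator could not separate oxygen from sham by such a grade in any case.

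Three further objections have some weight.

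- Criterion 3 in every category refers to the suspected intervention, so the scale is not worded for altitude throughout. This stands as a qualification, but criterion 1 still ties each category to altitude, and the mixed wording is itself inconsistent.
- The count of 3 depends on a strict reading, and the introductory wording of the categories leaves room for judgement. This also stands; step 3 gives the range. Two of the three unplaced combinations have no temporal link to altitude.
- Procedure harms are foreseen, minor and recorded as events whatever their grade. That is true, and no primary or secondary outcome uses the causality grade. It limits the consequence without supplying the missing scale.

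**Conclusion.** The point holds in a limited form. Section 7.3 requires a judgement about the treatment and supplies a scale tied to altitude, so for phase 2 oxygen/sham and for study procedures the required judgement has no applicable scale. The scale is also not exhaustive when read strictly (3 of 8 combinations unplaced), and its categories overlap when read loosely.

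The effect falls mainly on the grading of non-serious events. For serious events the problem is inconsistency: one event may be REMOTE under 7.3 and related under 10.2, and the Protocol does not say how the two connect. Reporting of SAEs and SUSARs is not blocked, and no efficacy conclusion is affected.

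This rests on two assumptions: that the must-have rules are meant literally, and that the AE page of the case report form, which is not at hand, follows section 7.3. It is an error in a stated rule rather than a detail left to an analysis plan, and it should be corrected.

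**What to change.** Reconcile section 7.3 with section 10.2:

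1. Grade relationship separately to (a) altitude, (b) study oxygen or sham in phase 2, judged blind, and (c) study procedures. Word the timing criterion for the exposure being graded.
2. Let POSSIBLE cover every event with reasonable timing that does not meet PROBABLE, including events with no alternative explanation or no known pattern.
3. Provide a category for all remaining events, so that every event receives exactly one grade for each exposure.
4. State in section 10.2 which grades, for any of (a) to (c), count as related.

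The cost is protocol wording and small changes to the AE page, plus a few more events graded as related. The blinded grade in (b) will not by itself separate oxygen from sham; the comparison by randomised period does that.

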### **Serious Adverse Event (SAE)**

Any untoward and unexpected medical occurrence or effect that:

- Results in death,
- Is life-threatening – refers to an event in which the subject was at risk of death at the time of the event; it does not refer to an event which hypothetically might have caused death if it were more severe,
- Requires hospitalisation, or prolongation of existing inpatients' hospitalisation,
- Results in persistent or significant disability or incapacity,
- Is a congenital anomaly or birth defect.
- Medical judgement should be exercised in deciding whether an AE is serious in other situations. Important AEs that are not immediately life-threatening or do not result in death or hospitalisation but may jeopardise the subject or may require intervention to prevent one of the other outcomes listed in the definition above, should also be considered serious.

SAEs will be immediately reported to the Ethics committee of the Canton Zürich. A special form will be completed.

An emergency action plan will be prepared with instructions on first aid and evacuation. In case of an emergency at Davos Jakobshorn the patient will receive first aid and treatment and will be evacuated to the hospital of Davos if necessary. Descent by cable car is available for emergencies also at night times. First aid materials will be readily available at all study locations. Light forms of Acute Mountain Sickness with symptoms such as headache, light-headedness, fatigue and insomnia may occur. More severe symptoms are unlikely because of the moderate altitude. Nevertheless, oxygen administration to reverse hypoxia and subsequent descent to lower altitude may be performed in case of emergencies. Skin irritation may appear due to attachments of the sensors. Arterial blood may cause minor pain and hematoma at the puncture site may occur. A first aid kit with medication for treatment of altitude related illness and for skin irritation and hematoma from puncture will be readily available.

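### Section 7.3 makes unexpectedness a condition of being a serious adverse event, which contradicts section 10.2; the ethics committee reporting times in the two sections also need to be linked.

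*Protocol*

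**What the plan says.** Section 7.3 (Serious Adverse Event) defines an SAE as "Any untoward and unexpected medical occurrence or effect that" meets one of the usual criteria: death, threat to life, hospitalisation, lasting disability or congenital anomaly. A last bullet allows medical judgement for other cases: "Important AEs that are not immediately life-threatening or do not result in death or hospitalisation but may jeopardise the subject". On reporting, the same section states: "SAEs will be immediately reported to the Ethics committee of the Canton Zürich".

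Section 10.2 (Reporting procedures) describes a sequence. First, "SAE's form will be completed and forwarded to the Principal Investigator within 24 hours". The principal investigator then judges two things: whether the event is related to the research procedures and whether it is unexpected, "i.e. an event that is not listed in the protocol as an expected occurrence". Finally, "Reports of suspected related and unexpected SAEs (SUSARs) will be submitted within 15 days and within 7 days for fatal or life-threatening SUSARs", and these go "to the Ethics Committee using the CIOMS format".

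**The concern.** Seriousness describes the outcome of an event. Expectedness asks whether the event was foreseen. Section 7.3 merges the two in the opening words of the definition, so *unexpected* governs every criterion below it, including death and hospitalisation. Someone must then decide whether an event was expected before knowing whether an SAE form is due at all.

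The stated purpose of the project is to provide a basis for counselling patients with COPD, PH and ILD about altitude travel, so a clear count of serious events matters. Section 12.1 allows for audits and inspections by public bodies but arranges no other independent monitoring, so correct classification rests largely on the written definition.

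**Working it through.** No arithmetic applies. The check sets the sections of the protocol side by side.

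**Step 1: what each section does with an event that meets a seriousness criterion.**

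| Event | Section 7.3, read literally | Section 10.2 |
|---|---|---|
| Unexpected and related | SAE; immediate report to the ethics committee | SAE form to the principal investigator in 24 hours; SUSAR; ethics committee within 15 days, or 7 if fatal or life-threatening |
| Unexpected, not related | SAE; immediate report to the ethics committee | SAE form in 24 hours; no expedited report specified |
| Expected | Not an SAE; no SAE form and no immediate report; recorded as an AE | SAE form in 24 hours; not a SUSAR |

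The third row is the contradiction. Judging expectedness in section 10.2 has a purpose only if some SAEs are expected, and under section 7.3 none can be. Section 10.2 also asks for non-serious events to be recorded whether expected or not, so it treats expectedness and seriousness as separate attributes.

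**Step 2: does the medical-judgement bullet repair the definition?** No. It stands under the same opening words, and it is written for events that fall short of death or hospitalisation. It does not bring an expected death or hospitalisation back in.

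**Step 3: which serious events would count as expected?** This cannot be settled from the text. Section 10.2 refers to events listed in the protocol as expected, but there is no list under that name. The nearest text, in section 7.3, says that light acute mountain sickness, skin irritation, and minor pain or haematoma at the arterial puncture site may occur, and calls more severe altitude symptoms unlikely. Elsewhere, section 4.2 (Withdrawal criteria) foresees significant acute mountain sickness, and section 9.1 foresees deterioration of the underlying illness, both as grounds for withdrawal. Two investigators could disagree on whether foreseeing an event in this way makes it expected. Under section 7.3 that disagreement would decide whether a hospitalisation is an SAE.

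**Step 4: what happens to an event that drops out?** Section 7.3 (Adverse Event) requires all clinical AEs to be reported on the AE page of the case report form, with intensity graded up to life-threatening and the relationship assessed. Worsening of a pre-existing condition is included. Section 10.2 adds that all adverse events are reported. The event keeps its record and loses its SAE label, SAE form and immediate report.

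**Step 5: reporting times.** The 24-hour rule concerns a different recipient, the principal investigator, and conflicts with nothing. The ethics committee has two rules: immediately for all SAEs, and within 15 or 7 days for SUSARs. Nothing says whether one is a first notice and the other the formal report.

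**The case against.** The strongest reply is that little harm follows in practice.

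- The events that section 7.3 itself says may occur are light and would rarely meet a seriousness criterion.
- The order of work in section 10.2 shows that the authors meant an SAE to be able to be expected.
- Every event stays in the adverse event record, and section 10.2 also promises interim and final reports to the ethics committee.
- The two reporting times are compatible in one sense: a report sent immediately also meets a limit of 15 or 7 days.

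Most of this stands, and it limits the point in four ways where a reader might go further.

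1. A reader might infer that severe altitude illness or a disease exacerbation is shut out of the SAE class. By the test in section 10.2 neither is listed as expected, and section 7.3 calls severe altitude symptoms unlikely, so both would still qualify as unexpected. The withdrawal criteria make their status arguable, but do not exclude them.
2. A reader might infer that the likeliest serious harms are the expected ones and vanish from view. The protocol names no serious harm as expected, and section 11.1 expects the eligibility criteria to prevent clinically relevant harm.
3. A reader might want to attach a percentage of patients to the loss. The protocol gives no SAE rate from which to derive one.
4. A reader might infer that section 10.2 lets only SUSARs reach the committee. It sets limits for SUSARs and is silent on other SAEs.

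The reply does not remove the contradiction. A definition should not rely on a later section to show that it means something else.

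**Conclusion.** The point holds as an error in the SAE definition. Taken literally, section 7.3 removes expected deaths and hospitalisations from the SAE class and from immediate ethics committee reporting, against the procedure in section 10.2. The size is qualitative: SAE labels and expedited reports are at risk, but adverse event data are not. Sample size, power and the 6-minute walk analysis are unaffected. The number of events involved is unknown and may be zero. It depends on how many serious events occur and on how site staff read *expected* without a labelled list.

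The reporting-time point is smaller. The two rules can be met together, but the text does not say how the reports relate.

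The conclusion assumes that staff would apply the definition as written. If they followed the sequence in section 10.2 instead, no event would be lost, but the two sections would still disagree.

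**What to change.** 1. In section 7.3, delete *and unexpected* from the opening words of the SAE definition, so that seriousness alone makes an SAE.
2. In section 10.2, keep expectedness and relatedness as judgements made after the SAE form is complete, and use them only to select SUSARs.
3. In both sections, use one statement on ethics committee reporting that says how the immediate SAE report and the 15-day or 7-day SUSAR report relate, for example whether the first is a notice and the second the full report.

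Because the section 10.2 test refers to events listed in the protocol, it would also help to label the list that is meant and to say whether events named as withdrawal grounds belong to it. What goes on the list is for the investigators to decide.

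The cost is a wording amendment, an aligned SAE form and possibly a few more forms to complete. This version is dated 13.12.2013, and the time table puts phase 2 in COPD and phase 1 in PH and ILD from 2014 on, so a change made at this version would be in place for those cohorts.
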